#### Organization of the day on the farm

After an initial welcoming phase in a dedicated “corner” according to the Montessori principles relating to the preparation of educational spaces, the day on the farm will be dedicated to the activities outlined in the participants’ individualized plans. Sharing lunchtime will become an opportunity to socialize with the farmer’s family and create important bonds that will allow older people to feel part of an equal and cohesive group. At the end of the day the staff will say goodbye and remind participants of the next scheduled meeting.

To reach the farms and then return to their homes, participants will be able to use a transport service arranged in collaboration with local service providers.

#### Staff dedicated to reception

The target user with Mild Cognitive Impairment is characterized by the absence of significant impact of the diagnosed condition on autonomy in daily life (26, 27). This makes it possible for participants to carry out daily activities in a condition of autonomy. The activities are organized and conducted by the owner of the farm and by a support figure, called facilitator, possessing skills in social farming and hospitality. Facilitators will be selected and trained prior to the start of the project. The facilitator participates in the management of the activities and completes the individual daily record with significant data. The facilitator works in close contact with the farm owner and with psychologists, gerontology experts, and specialists in the Montessori approach. Instead, INRCA experts and those from Montessori International Centre will be present on the farm only on some days for the initial and final evaluation of the subjects involved in the project, to monitor the progress of the activities and to carry out supervision meetings.

## Measures and outcomes

The primary outcome will be the assessment of the positive and negative affective states. As previously highlighted, increasing positive affect and reducing negative affect in older adults with MCI appears to be associated with better health and improved social relationships, both of which are important for enhancing cognitive reserve and mitigating the effects of neuropathology.

Secondary outcomes will be changes in the perception of physical and mental health as indicators of perceived quality of life and the maintenance of cognitive level in the project participants. Finally, to evaluate the feasibility of the project, participants’ and their caregivers’ satisfaction will be assessed with the project activities and a qualitative and quantitative evaluation of the quality of engagement in the project activities will be conducted including the number of subjects who join and those who withdraw from the project. Primary and secondary outcomes as well as clinical assessment are described in Table 2.

**Table 2 tab2:** Outcomes and clinical assessment.

Outcome	Clinical assessment
Primary outcome	
Affective states	Positive and Negative Affect Schedule (PANAS)
Secondary outcome	
Quality of life	Short Form health survey (SF12)
Cognitive status	Montreal Cognitive Assessment (MoCa)
Participants satisfaction	Two ad hoc structured questionnaires
Appreciation by family members	Ad hoc structured questionnaire
Quality of engagement in activities	Ad hoc sheet on “Treatment monitoring”

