### Positive and negative affect schedule (PANAS)

The Positive and Negative Affect Schedule (44) is a measure of self-reported affect which assess the two most general emotional dimensions that describe affective experience and subjective well-being. The PANAS consists of two scales which are composed of 10 items each: the Positive Affect scale (PA) reflects the level of pleasant engagement (e.g., feeling enthusiastic, excited, active and determined) and the Negative Affect scale (NA) reflects a general dimension of individual distress (e.g., feeling scared, nervous, guilty and ashamed). The PANAS scales show excellent psychometric properties.

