### Short form health survey (SF12)

The 12-item Short Form health survey, SF-12 (45–47), is a measure of health-related quality of life. It is an instrument with different weights for scoring physical and mental health, and measures health-related quality of life with 12 items categorized in eight areas: physical functioning, role physical, bodily pain, general health, vitality, social functioning, role emotional, and mental health. The raw scores of each item are coded, weighted, and summed into two scales: physical component summary score (PCS) and mental component summary score (MCS). Algorithms to calculate the value of the PCS and MCS indices of the SF-12 are available (47). Higher scores indicate better quality of life. The instrument will be used as in interviews.

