### Montreal cognitive assessment (MoCA)

The Montreal Cognitive Assessment is a rapid short screening test (5–10′) widely used to assess mild cognitive impairment (48). It assesses multiple cognitive domains: executive functioning, attention, language, memory, visuospatial skills, and orientation. In Italy, the MoCA has been adapted and standardized (49, 50). It offers the possibility of calculating both a total score and subscores for each domain. Standardized norms are available for both the total score and the domain-specific subscores.

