### Follow-up evaluation

The follow-up survey will take place at the end of the 3-month intervention and constitutes the final phase of the first cycle of prototype implementation. All measures from the initial screening will be repeated to check for any changes in the participants’ condition. In particular, it will be noted whether the subjective well-being has increased since the first survey, so whether the positive affects has increased and negative affects has decreased and if quality of life as increased. Moreover, it will be noted whether the participants and their caregivers are satisfied with the project through two *ad hoc* satisfaction questionnaires. This evaluation will be useful in order to identify any changes likely to improve the intervention.

Finally, after the three implementation cycles, the number of subjects who participated in one or more project cycles and the number of subjects who abandoned the project and the reasons for such dropouts will also be evaluated.

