### Statistical analysis

Data will be expressed by mean and standard deviation for continuous variables and by frequency and percentages for categorical ones.

Comparisons of all the scale variables of interest in the time (baseline vs. 3 months follow-up) will be performed using paired samples t test. We could also categorize some scales using specific cut-off and could evaluate if there has been a change of category over time by chi-square test for example.

Statistical significance will be set at *p* < 0.05.

All analyses will be performed using IBM SPSS Statistic for Windows, Version 24.0 (IBM Corp., Armonk, NY, USA).

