## Discussion

The aim of this study is to evaluate an individualized social intervention for individuals with mild cognitive impairment (MCI) in a farm-based setting. Research indicates that individuals with MCI can significantly benefit from proactive interventions that enhance the quality of their aging process, potentially reducing the risk of developing dementia while preserving their autonomy for as long as possible (10). Furthermore, literature suggests that promoting healthy aging in people with MCI requires more than just supporting their subjective well-being. It is essential to create an environment conducive to preventing or delaying the progression to dementia (10). Maintaining an active lifestyle—both cognitively and socially—is a crucial component of this approach, and the environment in which individuals with MCI engage should be structured to facilitate this goal (10, 28). In this context, the farms involved in the project provide a stimulating yet relaxing and non-medicalised environment, where participants can engage in a variety of therapeutic activities. Research suggests that the natural setting of the farm offers participants enjoyable and purposeful tasks, while also promoting greater autonomy and the freedom to make choices about their actions (16, 28). Additionally, taking part in social farming activities helps individuals develop a sense of accomplishment and satisfaction through the tangible nature of the tasks, as well as fostering a sense of belonging to a community where meaningful social connections can thrive (29). Consequently, in order to propose activities suitable for everyone and promote trust between peers, small homogeneous groups of individuals with MCI will be formed through the assessment of cognitive decline during the initial screening. Furthermore, the farms involved in the project will aim to promote people’s emotional well-being and quality of life through continuous engagement in daily life-related and meaningful activities by taking advantage of direct contact with nature, its slow rhythms and repetitive routines (28). The connection between the components of social agriculture and the Montessori principles will allow the project to promote activities well calibrated on the cognitive and psychosocial characteristics of each participant through careful observation. A recent review emphasizes how horticultural therapy, the Montessori methods for dementia, sensory and reminiscence therapies have many overlapping aspects and together they appear to be useful in decreasing agitation and improving the physical, cognitive, emotional and social functions of people with dementia (33). The configuration of an innovative service, both in terms of the approach to individuals with mild cognitive impairment and as a relief service for their family members, positions the farm as a key player in a new model of rural welfare. This model offers positive economic benefits for both the farms and public administrations through the optimisation of resources. Consequently, the Silver Agri Age project aims to establish an innovative pilot experience of social care for people with MCI, which can later serve as a best practice model to be extended to other farms looking to implement similar initiatives. While the sample size of 12 participants is relatively small, it is important to note that this is a pilot study, and as such, it is designed to serve as a foundation for future, larger-scale studies with an appropriately sized sample.

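### Every scale is tested at unadjusted p<0.05 in 12 uncontrolled participants, and nothing links the two primary PANAS scores to a conclusion; estimation should be the main output

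*Protocol article*

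**What the plan says.** Under Measures and outcomes, "The primary outcome will be the assessment of the positive and negative affective states"; Table 2 gives PANAS as the instrument. The PANAS section adds that "The PANAS consists of two scales which are composed of 10 items each", so the primary outcome is two scores. The secondary scales in Table 2 add the SF-12, whose items are "summed into two scales: physical component summary score (PCS) and mental component summary score (MCS"), and the MoCA, of which the article says "It offers the possibility of calculating both a total score and subscores for each domain".

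Follow-up evaluation says that it will be noted "whether the positive affects has increased and negative affects has decreased and if quality of life as increased". This gives a direction for each score and joins them with a conjunction.

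Statistical analysis compares all scale variables of interest between baseline and 3 months by paired t test. It adds optional category-change tests on some scales and sets one threshold for everything ("Statistical significance will be set at" p < 0.05). For description, "Data will be expressed by mean and standard deviation for continuous variables".

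The sample is 12, four on each of three farms, in one arm. Data collection says that no sample size calculation is planned. The Discussion calls the study a pilot "designed to serve as a foundation for future, larger-scale studies with an appropriately sized sample".

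**The concern.** Two sections treat the primary outcome differently. Follow-up evaluation describes improved affect as PA rising and NA falling. Statistical analysis tests each score separately at 0.05, and the article does not say how the two tests combine. As written, one significant PANAS score could be reported as a positive primary result while the other is flat or worse. The same holds for one significant score among all those tested.

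The opposite result is no easier to read. With 12 people, a p value above 0.05 is the more probable outcome even if there is a moderate true change, so it would say little against the intervention.

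The stake is modest but real. The pilot is meant to inform a larger, properly sized study, and a decision to go on, or to stop, could rest on p values that cannot carry it.

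**Working it through.** **Inputs from the protocol article**
- n = 12, single arm, paired comparison (Study population; Statistical analysis).
- 0.05 per test, no adjustment stated. Sidedness is not stated; two-sided is assumed.
- Primary scores: 2 (PA, NA). Main scores: 5 (PA, NA, PCS, MCS, MoCA total).
- The article gives no effect size, SD, correlation or dropout rate, so ranges are assumed below.

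The only stated figure is the sample size: 4 × 3 = 12, which is correct. It rests on farm capacity, so there is no power figure to reproduce.

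**1. Chance of at least one p<0.05 when nothing changes**

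For k independent tests the chance is 1 − 0.95^k. Counting only favourable changes, it is 1 − 0.975^k.

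| Scores | Any direction | Favourable only |
|---|---|---|
| One test | 5.0% | 2.5% |
| PA, NA (k = 2) | 1 − 0.95² = 9.8% | 1 − 0.975² = 4.9% |
| Five scores (k = 5) | 1 − 0.95⁵ = 22.6% | 1 − 0.975⁵ = 11.9% |

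Correlation between scores lowers these. In simulation (n = 12, paired t tests, common correlation 0.7), the any-direction chance is 8.5% for two scores and 15.5% for five. The favourable-only chance is 4.4% and 7.9%.

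**2. Power of one two-sided paired t test at 0.05**

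Noncentral t with n − 1 degrees of freedom and noncentrality d√n, where d is the mean change divided by the SD of change. For d = 0.5 and n = 12, the noncentrality is 0.5 × √12 = 1.73, the critical value is 2.20, and power is 35.3%.

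| Completers | d = 0.3 | d = 0.5 | d = 0.8 | d for 80% power |
|---|---|---|---|---|
| 12 | 15.8% | 35.3% | 71.4% | 0.89 |
| 10 | 13.6% | 29.3% | 61.6% | 1.00 |
| 8 | 11.4% | 23.2% | 49.6% | 1.16 |

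**3. What 12 people can estimate**
- 95% CI half-width for a mean change: 2.201 / √12 = 0.64 SD of change.
- 95% CI for the SD of change (chi-square, 11 degrees of freedom): √(11/21.92) = 0.71 to √(11/3.816) = 1.70 times the estimate.

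**4. Requiring both PA and NA to be significant**

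If both scores truly improve by 0.5 SD and are independent, the chance that both reach p<0.05 is 0.353² = 12%. By simulation it is about 19% if the improvements correlate at 0.5, and about 23% at 0.7.

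**The case against.** The strongest case against the point has four parts.

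- **Direction is stated.** Follow-up evaluation says which way each score should move, so a reader who infers that there is no success criterion at all goes too far. That stands. What is missing is any link between those directions and the tests.
- **Chance positives are not likely.** A reader might infer that they are. The figures are about 10% for the primary pair and at most about 23% over five scores: inflated, not probable. Since only favourable changes can support a claim of benefit, the primary figure falls to about 5%. That also stands, but the fair comparison is then 2.5% for a single two-sided test, so the risk is still about double.
- **The count should not be stretched.** Follow-up evaluation says that the screening measures are repeated. If MMSE, Tinetti, Barthel and IADL were also tested, nine independent tests would give 1 − 0.95⁹ = 37.0%. The article does not support that as the main figure: Table 2 lists none of the four as outcomes, and the follow-up list in Data collection names only PANAS, SF-12 and MoCA.
- **A declared pilot may be small, and an article may condense.** Low power contradicts no claim in the article, which explains the farm limit and lists the small sample and missing control group as limitations. An analysis plan that is not shown may hold a multiplicity rule, and not naming change scores or intervals is no error in itself. All of this stands. But the statistical section does state a rule, p<0.05 on every scale of interest, and the point is about that rule.

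**Conclusion.** The point holds in a limited form. The stated rule tests each score at unadjusted p<0.05 in 12 uncontrolled participants, and the joint wording for affect is not tied to it. With no true change, the chance of some p<0.05 is about 10% for PA and NA (about 5% favourable only) and up to about 23% over five scores (12% favourable only). Power for a 0.5 SD change is about 35%. Neither a lone significant score nor a non-significant one supports a conclusion about the intervention.

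The error rates assume two-sided tests and independence; correlation lowers them. The power figure assumes 12 completers and an effect size that the article does not give; losses lower it further. Nothing here makes the pilot invalid or its size wrong. Nor does it show that both PANAS scores must be significant: a reader might infer that from the conjunction in Follow-up evaluation, but that sentence sets no significance threshold.

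**What to change.** In Statistical analysis:

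- Label all tests exploratory.
- Make the main output for PA, NA, PCS, MCS and MoCA the mean change with its 95% CI, and the SD of change with its CI. The latter is what a larger study needs for sizing, and its interval (0.71 to 1.70 times the estimate at n = 12) shows how loosely it is known.
- State that no effectiveness claim will rest on a single p<0.05.
- State that any claim that affect improved will describe PA and NA together, in line with Follow-up evaluation.

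This changes wording only: no new data, visits or participants. The downside is that the pilot gives up significance claims. A mandatory rule that both PANAS scores be significant is not needed, since it would cut power at 0.5 SD from about 35% to about 12–23%.

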**Discussion and conclusion:**

During each three-month phase of the project different social farming activities will be proposed. Activities will also include sensory and cognitive stimulation and socialization within the farm. Since according to literature, participation in Montessori-based programs and exposure to nature generate positive effects, the emotional well-being of participants will be assessed as a primary outcome and life quality as a secondary outcome. Additionally, we believe that promoting participation in progressively challenging activities and autonomy may help stabilize cognitive decline. Therefore, cognitive level will also be assessed as a secondary outcome. Ultimately, the pilot study will provide insights into the possibility of integrating a prototype non-pharmacological intervention aimed at improving the well-being and quality of life of people with MCI into the dementia prevention service system.

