## Introduction

Rising life expectancy is contributing to a rapid increase in the number of older people worldwide and associated with a higher prevalence of chronic diseases such as dementia (1). According to the literature, dementia is one of the greatest global public health and social care challenges of our time and currently has no known pharmacological cure (1). This highlights the crucial role of prevention and non-pharmacological treatments as a strategy to address the emergency (1). American studies show that mild cognitive impairment (MCI) represents a transitional stage between healthy aging and dementia, affecting 10–15% of the American population over the age of 65 (2) and 19.7% of the global population over the age of 50 (3). In Italy, prevalence estimates vary from 3.2 to 24.5% in different studies (4). MCI is characterized by a slight impaired in one or more cognitive domains (e.g., memory, executive function, attention, language, and visuospatial skills), which does not interfere with psychosocial functioning and not meet the diagnostic criteria for dementia (5). According to the literature over 46% of individuals with MCI around the world progress to clinical dementia within 3 years (3). Moreover, studies on the American population indicate that approximately 8–15% of individuals with MCI progress to dementia every year, up to 80% develop dementia within 6 years (5). However, an Italian study found that 74% of individuals with MCI remained stable 1 year after diagnosis, and 10% reverted to normal cognitive functions (6). As a result, the National Dementia Observatory of the Italian National Institute of Health (ISS) has underlined the importance of promptly addressing this condition in order to delay its progression and conversion to dementia, thereby also reducing its social and economic impact (7). According to the literature it is possible to reduce – or at least delay – the risk of conversion from MCI to dementia by targeting a range of lifestyle-related risk factors, including levels of physical activity, social engagement, diet, mental well-being and cognitive stimulation (8–10). Recent MCI guidelines recommend group psychosocial interventions that support the adoption of healthier lifestyles to promote daily functioning and well-being in people with MCI (2). The guidelines also stress the importance of learning coping strategies that help people with MCI to relax and manage the challenges they face (2). In this context, the literature points out that spending time in natural environments offers individuals the opportunity to reflect on unresolved issues and to relax (11). These two responses – reflection and relaxation – may be considered valuable coping strategies for addressing the challenges associated with cognitive decline (2, 11).

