### Data collection

Subjects will be contacted to schedule a visit with the clinical team for screening evaluation. During the screening session, each subject will undergo the Mini Mental State Examination (39), Tinetti’s Scale (40), Barthel Index (41) and the IADL scale (42). Once the compliance with the study’s inclusion and exclusion criteria are verified and the informed consent is obtained, the team will proceed with the baseline assessment. As this is a pilot study, no sample size calculation is planned; pilot studies typically involve a limited number of participants — in this case, 12.

At baseline, demographic data will be collected, the Positive and Negative Affect Schedule (PANAS) and the SF12 questionnaire will be administered to evaluate participants’ quality of life. Furthermore, participants will undergo the Montreal Cognitive Assessment (MoCa) to assess cognitive status.

At follow-up, participants’ evaluation will be assessed by means of Positive and Negative Affect Schedule (PANAS), the SF12 questionnaire and the Montreal Cognitive Assessment (MoCa). Satisfaction with the project will be evaluated through two structured questionnaires administered to both participants and their caregivers.

The assessment will be carried out at the beginning and at the end of each quarter (see Figure 1).

The scales which will be used during the evaluations are described below.

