### Expected impact

#### Older adult participants

We anticipate that the individualized program will enhance the emotional well-being and quality of life for participants with MCI. By engaging in activities on the farm and sharing time with the diverse individuals who frequent it, participants will feel less isolated and more integrated into a group that genuinely values their experiences and opinions. Furthermore, we expect that participation in meaningful, purpose-driven activities, relevant to maintaining autonomy in daily life and adequately stimulating can keep their cognitive state stable and offer them the opportunity to redefine a purpose that animates their days. Studies show that having a purpose in life allows you to maintain your well-being and improve your quality of life (51).

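### Maintenance of cognition (MoCA) is a secondary outcome, but the only fixed test is a paired t test for difference, which cannot show maintenance

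*Protocol article*

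**What the plan says.** Under Measures and outcomes, the secondary outcomes include "the maintenance of cognitive level in the project participants"; Table 2 lists cognitive status, assessed by MoCA. Two other places give the same aim. The abstract's Discussion and conclusion says that the activities "may help stabilize cognitive decline. Therefore, cognitive level will also be assessed as a secondary outcome". The Expected impact section, on older adult participants, expects that suitable activities "can keep their cognitive state stable".

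The Statistical analysis section fixes one method for every scale: "Comparisons of all the scale variables of interest in the time (baseline vs. 3 months follow-up) will be performed using paired samples t test", with significance at p < 0.05. It adds a conditional option: "We could also categorize some scales using specific cut-off and could evaluate if there has been a change of category over time". No scale or cut-off is named for that option. The section mentions no confidence interval and no size of MoCA decline that would count against maintenance. Follow-up evaluation says which direction of change is sought for affect and quality of life, but gives no corresponding rule for cognition.

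**The concern.** The hoped-for result for cognition is no decline. A paired t test takes no change as its null hypothesis and can only produce evidence against it. Failing to reject is compatible with stability, and equally with a real fall that 12 people are too few to detect. The smaller or noisier the sample, the more often the test comes out non-significant, so imprecision works in favour of the hoped-for answer.

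What is at stake is the cognitive conclusion of the pilot. The article intends the study to inform dementia-prevention services and larger studies. As written, the plan gives no sound basis for saying that cognition was maintained.

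**Working it through.** **Plan's own figure.** There is none to reproduce. The article gives no SD, effect size, margin or power for MoCA and says that no sample size calculation is planned. The sample is 4 participants × 3 farms = 12.

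**Inputs from the document.** n = 12 (Study population); paired t test, baseline against 3 months, threshold 0.05 (Statistical analysis).

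**Assumptions, not in the document.** Two-sided test; SD of the paired MoCA change of 2 to 3 points, with 1.5 to 4 as a wider range; true mean falls of 1 and 2 points as illustrations. The document does not say what fall is clinically important.

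**Step 1: largest observed fall that stays non-significant.** This equals the half-width of the 95% CI:

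t(0.975, 11) × SD / √12 = 2.201 × SD / 3.464 = 0.635 × SD

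| SD of change | Limit (points) |
|---|---|
| 1.5 | 0.95 |
| 2 | 1.27 |
| 2.5 | 1.59 |
| 3 | 1.91 |
| 4 | 2.54 |

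**Step 2: how often a true fall gives p > 0.05.** Under a true mean fall D, the statistic follows a noncentral t with 11 df and noncentrality (D/SD) × √12. For D = 1 and SD = 2 this is 0.5 × 3.464 = 1.732, and power is 35%, so 65% of studies are non-significant.

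| SD of change | True fall 1 point | True fall 2 points |
|---|---|---|
| 1.5 | 44% | 1% |
| 2 | 65% | 12% |
| 2.5 | 76% | 29% |
| 3 | 82% | 44% |
| 4 | 88% | 65% |

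**Step 3: what a matching criterion could deliver.** Suppose maintenance is concluded only when the lower 95% limit of mean change lies above minus the margin (one-sided 0.025), and the true change is zero. The chance of reaching that conclusion with 12 people is:

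| SD of change | Margin 1 point | Margin 2 points |
|---|---|---|
| 2 | 35% | 88% |
| 2.5 | 24% | 71% |
| 3 | 18% | 56% |

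The two margins are illustrations only. A correctly framed analysis would therefore often end as inconclusive, and the estimate with its interval is the main usable result.

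**The case against.** The strongest reply is that the article nowhere says a non-significant p will be taken as stability. It states no formal hypothesis for MoCA, and the remark on stable cognition under Expected impact is an expectation, not a success rule. That is right. A reader might infer that a real loss would be reported as maintained cognition, but this is only an inference from the absence of another criterion. The mismatch between the stated outcome and the stated test does not depend on it.

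A reader might also conclude that the plan cannot fail on this outcome. The document does not support that. Means and SDs will be reported, so a fall would be visible, and at SD 2 to 3 a true 2-point fall is detected in 56% to 88% of studies (100% minus 44% and 12%). Visit-level means and SDs do not, however, give the SD of the paired change, so on their own they do not yield the interval.

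It is tempting to add that stability is expected anyway, because "an Italian study found that 74% of individuals with MCI remained stable 1 year after diagnosis, and 10% reverted to normal cognitive functions" (74% + 10% = 84%). That figure classifies individuals at one year in one study. It is not a mean MoCA change at 3 months, and the same Introduction cites other studies with substantial progression. Dementia conversion is not an outcome here either, so the yearly progression rates do not bear on this test.

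The Limitations section already acknowledges the small sample and the missing control group, so neither is a new point. Finally, a formal margin in an unpowered 12-person pilot is debatable, and its value might be left to a fuller document. That argues for a light remedy. It does not reconcile the test with the outcome, because this article states both.

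**Conclusion.** The point holds in a limited form. The article names maintenance of cognition as an outcome and fixes a test that cannot support a conclusion of maintenance. The only alternative it offers is optional and unspecified, and it too looks for change.

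At an assumed SD of change of 2 to 3 points, a true 1-point mean fall goes undetected in 65% to 82% of studies of this size (44% to 88% over SD 1.5 to 4), and a true 2-point fall in 12% to 44%. These figures rest on the assumed SD, a two-sided test and all 12 participants completing. The mismatch itself needs no assumption. Severity is minor to moderate: it concerns one secondary outcome and leaves the primary affect analysis and the feasibility aims untouched.

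**What to change.** In Statistical analysis:

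- Report the mean MoCA change from baseline to 3 months with its 95% CI. Give the same descriptively at the later end-of-quarter assessments already planned under Data collection.
- State that p ≥ 0.05 will not be taken as maintenance.
- Before follow-up data are seen, have the investigators specify the MoCA decline they regard as important. Describe cognition as maintained only if the CI excludes a decline of that size, and otherwise as inconclusive.

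This needs no new data, visits or participants, only a few sentences and one decision on the size of decline. The price is that the result will often be inconclusive, which is the accurate description of what 12 people can show.
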